### Randomisation

The following randomisation mechanism will be applied: cards marked “intervention group” or “control group” will be prepared, in quantities corresponding to the numbers required for each group. These cards will be placed in sealed opaque envelopes, which will be shuffled and then numbered, such that none of those involved will know the group to which each envelope corresponds. Each of the participants will be assigned a participation number (by order of entry to the study). The researcher responsible for the randomisation will open the envelope when the patient/caregiver confirms their intention to participate. This system ensures that the group sizes foreseen will be achieved and that the assignation to the study groups is unlikely to be manipulated.

Each eligible patient in palliative care and, if applicable, their caregiver will be invited to participate in the study. If they both accept, a single envelope will be used for both persons (i.e. both will be in the same group, control or intervention). If only one accepts, they will also be given an envelope assigning them to the control or the intervention group. Participants will continue to be assigned until the pre-established sample size is reached.

When the researcher performing the randomisation opens the envelope and is aware of which group the patient (and caregiver, if applicable) belongs to, they will be informed of the corresponding procedure that will be applied, without mention of whether this refers to a control or an intervention group. The same researcher will instruct the participant in the use of the mp3 player to access an audio file through Google Drive or in the use of the Spotify app on the mobile phone, as the case may be. The participant will also be asked not to perform any activity other than listening during the intervention, and not to let the evaluator know what they have heard, explaining that this restriction will help make the research data more reliable.

If the patient is a member of the intervention group, in addition to the above, the researcher will ask them to make a list (at home) of 15 songs or musical items that put them in a good mood, and to send it (by mail or by phone) to the researcher so that the titles selected can be obtained and made ready for the beginning of the sessions, available either on the mp3 player or through the music app of the mobile phone. Participants in the control group will listen to health education advice, on the mp3 player or via Google Drive on their mobile phone.

The case management nurses at the six healthcare centres collaborating with this study will evaluate the study variables at three time points: 1 day before the participant receives the music delivery system from the researcher, 7 days after the intervention and 30 days after the intervention. These nurses will be blinded to the study group to which the participant is assigned.

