## Methods / design

### Study design

The study will take the form of a randomised controlled trial (RCT), double blinded and multicentre, with a study population composed, on the one hand, of cancer patients receiving at-home palliative care and, on the other, of their informal caregivers. In each case, two parallel groups will be considered: a control group (CG) and an experimental group (EG).

The study will be conducted at six Primary Care Clinical Management Units: Puerta Blanca, Tiro de Pichón, Nueva Málaga, La Luz, Palma-Palmilla and Rincón de la Victoria Basic Zone, all within the Málaga-Guadalhorce Health District.

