### Sample size

The most significant variable in palliative care patients is assumed to be anxiety. In a review conducted by Bradt et al. [29], this variable presented a distribution with a standard deviation of 1.8, for a population similar to that considered in the study we propose, albeit with a wider range of results. Previous studies have reported that music therapy has a significant impact on this variable. In one case, an effect size of 7 was measured (effect size of 29% of the standard deviation). Another study, of cancer patients receiving treatment including ginseng [39], recorded a variation of 0.83 points on the Edmonton scale, with a standard deviation of 2.34 (35% of the standard deviation). Assuming a 2-point decrease in before-after anxiety to be clinically relevant, and a maximum standard deviation of 2.5 in our population, with an alpha error of 0.05 and a beta of 0.10, we calculate that two samples of 33 subjects will be necessary, to enable the option of a 1:1 ratio between the samples. For convenience, and to allow for losses to follow up, this sample size will be increased by 20%, to two samples of 40 persons. The Epidat 4.2 statistical program was used to perform these calculations.

Hanser et al. [40] recorded an increase in caregivers’ satisfaction following the incorporation of music therapy into the healthcare provided, with a standard deviation of 1.33 for relaxation, 1.87 for comfort, and 1.23 for happiness. Taking into account these findings and assuming an increase of one point in the dimension of caregiver happiness to be clinically relevant, we calculate that two samples of 34 caregivers will be necessary. For convenience, this sample size will be increased by 20%, to two samples of 41 persons, to allow for losses to follow up.

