### Statistical analysis

A descriptive study will be made of the variables collected, calculating the mean and standard deviation in each case for the normally-distributed continuous variables, the confidence interval as appropriate for specific estimates, the median and interquartile range for non-normally-distributed continuous variables, and frequencies and percentages for categorical variables. The normality of the distribution will be determined by the Shapiro-Wilk test. Baseline values for the two groups will be compared.

The before and after-intervention values, in the control and intervention groups, will be compared by Student’s t-test for related samples in the case of normal continuous variables, and by the Wilcoxon T-test for paired data in the case of non-normal continuous variables.

In addition to this bivariate analysis, a multiple linear regression will be performed, in which the following dependent variables will be addressed, depending on the case: pain, fatigue, nausea, depression, anxiety, drowsiness, dyspnoea, anorexia, sleep disorders, malaise/well-being and quality of life. The independent variables considered will include both the intervention itself and also the participants’ sociodemographic variables (sex, age, level of education, marital status) and clinical variables (pathology, total time receiving palliative care). A similar procedure will be followed to determine the significance of the consumption of analgesics and the number of visits made by the nurse. All results obtained will be presented at a confidence interval of 95%. Thus, *p* < 0.05 is assumed to be statistically significant. The statistical software SPSS 23 and Epidat 4.2 will be used in this analysis.

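### All six centres draw from one shuffled envelope sequence and centre is not a named covariate: a modest loss of precision and a risk of chance imbalance, not a systematic bias

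*Protocol article*

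**What the plan says.** Under Study design: "The study will be conducted at six Primary Care Clinical Management Units". The Randomisation section adds: "The case management nurses at the six healthcare centres collaborating with this study will evaluate the study variables at three time points".

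The same section sets out the allocation step by step. Cards are made "in quantities corresponding to the numbers required for each group", and then: "These cards will be placed in sealed opaque envelopes, which will be shuffled and then numbered". Participation numbers follow the order of entry to the study, not the order within a centre. A patient and caregiver who both accept share one envelope. The only balance claimed is in the overall group sizes.

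Under Statistical analysis, the regression contains the intervention and these covariates: "sex, age, level of education, marital status) and clinical variables (pathology, total time receiving palliative care". Neither centre nor evaluator is named. The section continues: "A similar procedure will be followed to determine the significance of the consumption of analgesics and the number of visits made by the nurse".

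**The concern.** Centre can influence outcomes here in two ways.

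- **Measurement.** The natural reading is that each centre's nurses evaluate that centre's participants. The Caregiver Strain Index (CSI), the caregivers' primary outcome, is taken by semi-structured interview, so interviewer style could matter.
- **Local practice.** Case manager home visits and staff time on telephone calls are counted as resource use and feed the cost-utility analysis. Nurse visits and analgesic use are also tested in their own right.

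With about 80 patients over six centres, a single shuffle can leave a centre lopsided. Any difference between centres then enters the arm comparison by chance. If centre is left out of the model, between-centre variation also stays in the error term. What is at stake is precision, and the credibility of a result in which one centre happens to be mostly one arm.

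**Working it through.** **Inputs from the article (Sample size):** target difference 2 points on anxiety ("Assuming a 2-point decrease in before-after anxiety to be clinically relevant"), SD 2.5, alpha 0.05, power 0.90, 33 per arm, raised to 40.

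**Assumptions (not in the article):** near-equal centres (14, 14, 13, 13, 13, 13 patients), and an intraclass correlation (ICC), the share of variance due to centre, of 0 to 0.20.

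**1. The plan's own figure.** n per arm = 2 × (1.960 + 1.282)² × 2.5² / 2² = 32.8, so 33. Then 33 × 1.2 = 39.6, so 40. Both reproduce with a two-sided test. The point does not change the sample size.

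**2. How lopsided centres become.** With 40 of 80 patients in each arm, the number in one arm at a 13-patient centre is hypergeometric (80, 40, 13). The probability of a 9:4 split or worse is 0.22. In 40,000 simulated shuffles, at least one of the six centres split 70/30 or worse in 41% of trials. With the cut-off at 9:4 (10:4 for centres of 14), the figure is 69%. These figures count lopsided centres; they do not measure error in the estimate.

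**3. Error in the estimate.** Let D be a centre's surplus of one arm divided by 40. The variance of the surplus at a centre of size n is n(80 − n)/79, which is 11.03 for n = 13 and 11.70 for n = 14. Summed over centres: (4 × 11.03 + 2 × 11.70) / 40² = 0.0422, with square root 0.205. The centre SD is 2.5 × √ICC, so the SD of the shift is 0.205 × 2.5 × √ICC:

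| ICC | Centre SD | SD of shift | 95% of absolute shifts below (simulated) |
|---|---|---|---|
| 0.01 | 0.25 | 0.05 | 0.10 |
| 0.05 | 0.56 | 0.12 (0.115) | 0.24 |
| 0.10 | 0.79 | 0.16 | 0.33 |

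The shift averages zero. For comparison, the standard error of the arm difference is 2.5 × √(2/40) = 0.56 at 40 per arm and 2.5 × √(2/33) = 0.62 at 33 per arm. The simulated type I error without a centre term is 0.045–0.052.

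**4. What a centre term and stratification do to the interval.** Take 33 per arm and six centres of 11. Three factors change the width relative to the unstratified, unadjusted analysis:

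- *Residual SD:* √[(1 − ICC) / ((1 − ICC) + 0.846 × ICC)], where 0.846 = (66/65) × (5/6). This is 1.000, 0.978, 0.956 and 0.909 at ICC 0, 0.05, 0.10 and 0.20.
- *Degrees of freedom, 64 to 59:* t ratio 2.0010/1.9977 = 1.0016.
- *Balance within centres:* if stratified (6:5 in each centre), √[16.5 / (6 × 30/11)] = 1.004. If unstratified, about √(65/60) = 1.041.

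| ICC | Stratified and adjusted | Unstratified, centre term only | Simulated power, unstratified: without → with centre |
|---|---|---|---|
| 0 | 0.6% wider | 4% wider | 0.89 → 0.86 |
| 0.05 | 1.6% narrower | 2% wider | 0.89 → 0.88 |
| 0.10 | 3.8% narrower | unchanged (0.3% narrower) | 0.90 → 0.90 |
| 0.20 | 8.6% narrower | 5% narrower | 0.90 → 0.93 |

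Simulation of interval widths agrees with these factors to within about 0.2 percentage points.

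**The case against.** Concealed, unstratified 1:1 allocation is a valid design, and chance imbalance by centre does not bias it. The unadjusted standard error already allows for that imbalance, which is why the type I error is held. This stands, and it limits the point to precision.

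The covariate list is worded as what the model will include, so it is not closed, and a centre term is commonly left to an analysis plan that is not shown. This also stands: a reader might infer that an imbalance can be neither prevented nor corrected, but only the first half follows from the article. The allocation mechanism is different, because it is described in full and has to be fixed before enrolment.

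The rater argument is weak for the patients' primary outcome, since patients choose their own ESAS scores. The CSI consists of true-false items, evaluators are stated to be blinded, and stable interviewer differences partly cancel in before-after comparisons. All six units lie in one health district and follow the same regional plan, so large differences in practice are possible but not documented. The argument is therefore stronger for strain, visits and costs than for symptoms.

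It is also tempting to quote the 69% as the size of the problem, or to claim 2.5–5% narrower intervals from 1 − √(1 − ICC). The first depends on the cut-off and measures no error. The second ignores the lost degrees of freedom and the imbalance that remains when only a model term is added.

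**Conclusion.** The point holds as an optional, low-cost improvement. The article fixes one unstratified sequence for six centres and does not name centre in the model, although centre may affect interview-based strain, visits, telephone time and costs. A reader might infer that the treatment effect is biased; the documents do not support that. At an ICC of 0.05–0.10, the chance shift in anxiety (SD about 0.12–0.16 points) is roughly a quarter of the standard error and under a tenth of the 2-point target.

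The size rests on the assumed ICC and near-equal centres. Markedly unequal centres would change the figures. For visits and costs, the article gives no variance from which to compute an effect.

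**What to change.** If allocation has not started:

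- **Randomisation:** prepare a separate numbered envelope set for each centre, in shuffled blocks of varying, undisclosed size. Keep one envelope per patient-caregiver pair.
- **Statistical analysis and Economic evaluation:** include centre in the between-arm models for symptoms, CSI, visits, medication and costs. The CSI is not among the regression outcomes now listed, so it has to be named.

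The cost is six envelope sets instead of one and five degrees of freedom. Arm totals may differ by a few, which gives up the exact group sizes that the present scheme guarantees. Allocation also becomes somewhat more predictable within blocks, hence the varying and undisclosed block sizes. The sample size stays at 33 per arm before losses.

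If allocation is already complete, a centre term alone gives no gain for symptoms unless the ICC exceeds about 0.10. It is then best prespecified as a sensitivity analysis.

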### Outcome assessment

The primary outcome measures that will be considered to assess the effectiveness of the intervention are the symptoms presented by the patients and the degree of overload experienced by the caregivers. The secondary outcomes considered, for patients and caregivers, are health-related quality of life, satisfaction with the intervention and the economic valuation. The outcome measures will be obtained from questionnaires completed at the start of the study (t0), at 1 week after randomisation (t1) and at 1 month after the start (t2).

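### The baseline assessment (T0) is tied to receipt of the device rather than placed before allocation, so self-reported baseline scores can be taken after participants know their procedure

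*Protocol article*

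**What the plan says.** Four statements in the protocol article bear on the timing of T0.

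- **Allocation** (Randomisation): the researcher "will open the envelope when the patient/caregiver confirms their intention to participate". No assessment is named as a precondition.
- **Disclosure** (Randomisation): once the envelope is open, "they will be informed of the corresponding procedure that will be applied, without mention of whether this refers to a control or an intervention group". Although the label is withheld, the participant learns whether they will hear music or spoken education.
- **Preparation, music arm only** (Randomisation): "the researcher will ask them to make a list (at home) of 15 songs or musical items that put them in a good mood". The list goes to the researcher by mail or phone "so that the titles selected can be obtained and made ready for the beginning of the sessions".
- **Baseline** (Randomisation): the case management nurses carry out the first assessment "1 day before the participant receives the music delivery system from the researcher", with later assessments 7 and 30 days after the intervention.

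The Outcome assessment section gives a second schedule. There the questionnaires are "completed at the start of the study (t0), at 1 week after randomisation (t1) and at 1 month after the start (t2"). Table 1 labels its columns T0, T1 at 7 days and T2 at 30 days, and does not say from what point the days are counted.

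**The concern.** A baseline should be a value that allocation cannot have influenced. The surest way to achieve this is to collect it before anyone on site, and above all the participant, can act on the allocation. Here the anchor is delivery of equipment, an event that follows allocation in at least some cases and whose date may depend on the arm.

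Blinding of the nurses does not remove the problem. ESAS is the patient's own 0 to 10 rating of each symptom, and CSI is built from the caregiver's own true-false answers. Someone who has just been told what they will listen to, or who has spent time picking music that lifts their mood, may answer differently.

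The Statistical analysis section uses T0 as the before value in paired tests within each group and compares baseline values between groups. EQ-5D-5L, the source of the QALYs, is collected at T0 as well. A T0 affected by disclosure would therefore reach the before-after results and the baseline comparison, and could reach the cost-utility analysis.

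**Working it through.** The main check is the order of events. No figure in the plan depends on it.

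**1. Where T0 falls relative to the envelope.** Call the day the envelope is opened day 0, and let the device be received on day *R*. The stated rule puts T0 on day *R* − 1. The article never gives *R*, so there are three cases:

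- *R* = 0 in both arms (handover at the same contact): T0 is on day −1, before allocation. There is no problem.
- *R* of 2 or more in both arms: T0 is on day 1 or later, after allocation and disclosure. With *R* = 1, T0 is on day 0 and the order within the day is undefined.
- *R* differs by arm: the lag from allocation to T0 differs by *R*(music) − *R*(control). If control participants receive the device on day 0 and music participants on day 2 or later, T0 precedes allocation in one arm and follows it in the other.

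The music arm has steps that the control arm lacks: writing 15 titles at home, sending them, and having them obtained and loaded. The control recording is a common audio file that needs no personal selection. A player already holding the chosen titles cannot be received on day 0. That makes a later *R*, and hence a T0 after disclosure, probable in the music arm.

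**2. Whether the second schedule settles it.** Let the first session be on day *d*. Seven daily sessions end on day *d* + 6.

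- Outcome assessment puts T1 on day 7. For all sessions to be finished by then, *d* + 6 ≤ 7, so *d* ≤ 1. The list would have to be written, sent and prepared within about a day.
- Randomisation puts T1 7 days after the intervention. That is day *d* + 13 if counted from the last session, or *d* + 7 if counted from the first. With *d* = 1 these are day 14 and day 8, against day 7 above.

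The two schedules disagree on T1. For T2, one counts from the start and the other from the intervention. Start of the study is not defined relative to the envelope, so it does not place T0 before allocation either.

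**3. What a shift would do (illustration).** Let disclosure shift mean T0 anxiety by *s* points in one arm, with T1 unaffected. The documents give no value for *s*, so a range is shown.

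- That arm's mean before-after change moves by *s*, and so does any between-arm difference in change.
- A baseline-adjusted comparison with slope *b* moves by *b* × *s*; *b* = 0.5 is assumed.

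| Assumed *s* | Shift in change | As share of 2 points | Shift if adjusted (*b* = 0.5) | As share of 2 points |
|---|---|---|---|---|
| 0.25 | 0.25 | 12.5% | 0.125 | 6.25% |
| 0.5 | 0.5 | 25% | 0.25 | 12.5% |
| 1.0 | 1.0 | 50% | 0.5 | 25% |

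The 2 points is the before-after anxiety change that the Sample size section treats as clinically relevant.

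Only the first effect, on an arm's own before-after change, applies directly to the paired tests in the Statistical analysis section. That section names no between-arm change-score test, and its listed regression covariates do not include the baseline score. If the regression outcome is the follow-up score, a shift at T0 does not enter it.

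**The case against.** The strongest reply is that the sequence is inferred. The handover date is never stated. The researcher who opens the envelope also teaches the participant to use the player or app, which fits handover at that same contact; T0 would then fall the day before allocation. The titles need only be ready by the first session, not by receipt of the device, and a participant using the app on their own phone needs no loaded player. The flow chart is not available here and may place baseline explicitly. All of this stands, and it is why the point is that T0 **can** follow disclosure and **probably** does in the music arm. A reader might infer that T0 is definitely measured after the song list is made; the documents do not support that.

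It could also be said that a condensed article leaves visit order to the full protocol. That would answer silence, but the article states a specific anchor, and two of its sections give different schedules.

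On direction, anticipation in the music arm would lower T0 symptoms and disappointment in the control arm would raise them. Both would understate a benefit of music. This is plausible but not assured: the Background cites a study in which music sometimes reminded patients of their altered state, which would push the other way. The one-week recall of ESAS would dilute a reaction to very recent news, but with a longer lag it would take in more days after disclosure.

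A reader might also infer unequal death or withdrawal before T0. No lag is given and patients expected to live only a few days are excluded, so this is a possibility without a size.

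Finally, the present anchor keeps the interval from T0 to device receipt equal across arms, and the fix gives that up. This is a real cost.

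**Conclusion.** The point holds as a weakness in a stated rule. The article anchors T0 to device receipt, opens the envelope and explains the procedure at confirmation, and nowhere requires T0 to come first. A self-reported baseline taken after disclosure is therefore permitted in both arms and likely in the music arm, possibly at a different lag by arm. The two schedules for T0, T1 and T2 also need to be reconciled.

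The size and direction of any bias in before-after change are unknown. The 0.5-point shift, and the 25% and 12.5% that follow from it, are illustrations. They rest on an assumed shift confined to T0 in one arm, and the second also on an assumed slope in an adjusted analysis that the plan does not specify. They should not be read as estimates of bias in this trial, and the documents do not show that its baseline is invalid. The change is worth making because it is cheap and removes the question.

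**What to change.** Replace the device-receipt anchor with one rule for both arms: the nurse completes all T0 instruments after consent and before the envelope is opened. Where patient and caregiver share an envelope, both complete T0 first. The researcher opens the envelope only once T0 is confirmed complete.

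Then state one origin for T0, T1 and T2, and use it in the Randomisation section, the Outcome assessment section and Table 1. Say whether T1 and T2 are counted from randomisation, from the first session or from the last session.

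The cost is a reordering of an existing assessment and some coordination between nurse and researcher; no procedure is added. The downside is that the interval from T0 to the first session may be somewhat longer in the music arm while the songs are prepared, and symptoms can change in that time. Record the dates of T0, envelope opening, device receipt and first session, and report the T0-to-first-session interval by arm.
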